### Secondary outcomes

The individual components of the primary outcome: time to death (all causes) or transplant and time to first non-elective hospital admission will be analysed separately as secondary outcomes. In addition, respiratory-related events will be analysed separately from non-respiratory-related events. The following measurements will also be undertaken at baseline, 3 and 6 months post randomisation, then 6-monthly for the duration of the trial plus at the end of trial/hospitalisation.

### Health-related quality of life

This is being assessed in a number of ways: (1) the King’s Brief Interstitial Lung Disease (K-BILD) health-related quality of life questionnaire [21] which is the only validated ILD-specific instrument. This 15-question, self-completed patient questionnaire has a mean score of 53 (standard deviation 26) units in IPF and a minimum clinical significant difference of 8 units; (2) the MRC Breathlessness Score [16] which is the most widely utilised dyspnoea score for patients with ILD; (3) the EuroQol 5-dimension (EQ5D) questionnaire [22] will be used to determine quality-adjusted life years (QALYs) but a cost-utility analysis will not be undertaken. The K-BILD does not specifically capture cough so we are assessing cough using a Visual Analogue Scale. Overall, quality of life is being captured using a 6-point Likert global rating of concept scale.

### Lung function

Spirometry [23] and the total lung-diffusing capacity of carbon monoxide (DLCO) [24] are being measured according to current American Thoracic Society/European Respiratory Society guidelines. FVC and DLCO are both components of prognostic modelling algorithms [25], are frequently utilised in clinical trials [9] and are part of routine care.

### Peripheral blood

Peripheral blood is being taken at baseline, 3, 6 and 12 months and at the end of the trial and stored for analysis of measures of (1) infection/inflammation, including C-reactive protein (CRP), which is an acute-phase serum protein that is increased in concentration in patients with inflammation and is a significant prognostic indicator for survival in patients with IPF [26]; (2) alveolar epithelial injury including surfactant protein (SP)-D which is elevated in serum in patients with IPF [27] and predicts mortality [28] and matrix metalloproteinase (MMP)-7 which is related to disease severity [29, 30] and is an independent predictor of mortality [31] and (3) neutrophil activity, including myeloperoxidase, which is almost exclusively expressed in neutrophils and is a marker of their activation and degranulation.

### Routine microbiology

Sputum is being obtained, where possible, and sent for local microbiological culture and susceptibility testing; and a nasal swab will be sent for viral culture, if clinically indicated, in all patients.

### Biomarkers

Alveolar epithelial cell injury markers (SP-D, MMP-7) will be measured as for peripheral blood samples. Neutrophil elastase is indicative of neutrophil activation and is related to disease activity in IPF [32]. Neutrophil elastase inhibitors have been shown to reduce the development of pulmonary fibrosis in animal models [33]. Elastase activity will be measured using the EnzChek elastase assay (Molecular Probes). Pro-collagen III *N*-terminal peptide (PIIINP) is a collagen turnover peptide and a surrogate marker of fibrosis. It is elevated in patients with IPF [34] and is higher in patients with progressive and non-progressive IPF [35].

### Measurements during the first non-elective admission

Patients are being asked to carry a card detailing their involvement in the trial and their local investigator contact details. This is for safety reasons and in order to maximise ascertainment of follow-up during hospital admission. Questionnaires, blood samples and routine microbiology are being collected in the same manner as undertaken at the routine visits.

### Safety outcomes

Blood for full and differential white cell counts, urea and electrolyte assays and liver function assessment is being taken at baseline, 6 weeks, 3, 6, 9 and 12 months then 6-monthly for the duration of the trial and at the end of trial/hospitalisation. The 6-week and 9-month blood tests may be taken in primary care, with assessment of adverse events being captured by phone.

### Adverse events

This trial complies with UK NHS Research Ethics Service guidelines on reporting of adverse events (National Research Ethics Service Safety and progress reports (Clinical Trials of Investigational Medicinal Products (CTIMPs)); http://www.hra.nhs.uk/research-community/during-your-research-project/safety-reporting/). As hospitalisation and death are outcome variables they will only be regarded as serious adverse events if they are drug related.

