**Methods/design:**

The EME-TIPAC trial is a double-blind, placebo-controlled, randomised, multicentre clinical trial.

A total of 330 symptomatic patients, aged 40 years old or older, with IPF diagnosed by a multidisciplinary team (MDT) according to international guidelines and a FVC ≤ 75% predicted will be enrolled. Patients are randomised equally to receive either two tablets of co-trimoxazole 480 mg or two placebo tablets twice daily over a median treatment period of 27 (range 12–42) months. All patients receive folic acid 5 mg daily whilst on the trial IMP to reduce the risk of bone marrow depression.

The primary outcome for the trial is a composite endpoint consisting of the time to death, transplant or first non-elective hospital admission and will be determined from adverse event reporting, hospital databases and the Office of National Statistics with active tracing of patients missing appointments. Secondary outcomes include the individual components of the primary outcome, (1) King’s Brief Interstitial Lung Disease Questionnaire, (2) MRC Dyspnoea Score, (3) EQ5D, (4) spirometry, (5) total lung-diffusing capacity and (6) routine sputum microbiology. Blood will be taken for cell count, biochemistry and analysis of biomarkers including C-reactive protein and markers of disease.

The trial will last for 4 years. Recruitment will take place in a network of approximately 40 sites throughout the UK (see Table 1 for a full list of participating sites). We expect recruitment for 30 months, follow-up for 12 months and trial analysis and reporting to take 4 months.

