## Methods/design

The trial is a phase III, double-blind, parallel-group, 1 to 1 randomised, placebo-controlled, multicentre clinical superiority trial of orally administered co-trimoxazole versus placebo in patients with moderate to severe (FVC ≤ 75% predicted) IPF, with outcomes assessed over a median treatment period of 27 (range 12–42) months. Participants receive co-trimoxazole or placebo until they meet a primary endpoint event, they withdraw consent, or the trial concludes. This trial is designed to align with routine care as much as possible and the trial visits are intended to coincide with routine clinical follow-up visits. Follow-up of assessment measures will continue for the duration of the trial for those participants stopping trial medication due to adverse events or patient choice. The vital status and details of admission to hospital will be captured for all patients who have consented to participate in the trial regardless whether they have withdrawn from the intervention or trial assessments.

Figure 1 provides a study flowchart of the trial design and Fig. 2 provides the time and event schedule. The trial protocol (v3.0, dated 16 May 2016) is based on the Standard Protocol Items: Recommendations for Interventional Trials (SPIRIT) 2013 Statement for protocols of clinical trials (see Additional file 1).

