Patients with a FVC of more than 75%, as predicted based on the algorithm suggested by Crapo et al. [17] are not recruited into the trial; this is intended to exclude patients with mild disease and, instead, to identify patients more likely to meet the primary endpoint (see ‘Sample size’ section). Other reasons for exclusion include (1) a recognised significant co-existing respiratory disease, e.g. obstructive airways disease (defined as forced expiratory volume in 1 s (FEV_1_)/FVC < 60% [18]), (2) a significant medical, surgical or psychiatric condition that would affect subject safety or influence the trial outcome or (3) untreated folate or vitamin B_12_ deficiency, to ensure that no bone marrow or neurological adverse effects occur with folate therapy to vitamin B_12_-deficient individuals. Sulphonamides are recognised to increase the risk of haemolysis in individuals with glucose-6-phosphate dehydrogenase (G6PD) deficiency although this risk remains low [17]. The prevalence of G6PD deficiency is higher in men of African, Asian or Mediterranean descent and, therefore, patients in these demographics are screened for the condition and, if found to have G6PD deficiency, are excluded from the trial. Patients with a self-reported respiratory tract infection within 4 weeks of screening (defined as two or more of cough, sputum or breathlessness and requiring antimicrobial therapy) are not eligible due to the difficulty of obtaining reliable baseline lung function. Those patients receiving a short course of antibiotics (for any indication) within 4 weeks of screening or long-term prophylactic antibiotic treatment (defined as more than 1 month of therapy) within 3 months of screening are also ineligible as this may have an impact on lung microbiota. A risk of sudden death in patients treated with co-trimoxazole and angiotensin-converting enzyme (ACE) inhibitors was identified [19] and is thought to be due to an increase in serum potassium due to an amiloride-like action of trimethoprim on sodium channels in the distal nephron [20]. For this reason, patients with a serum potassium greater than 5.0 mmol/L are excluded and patients with a baseline serum potassium of between 4.7 and 5.0 mmol/L, who are 66 years old or over and taking potassium-sparing diuretics (including ACE inhibitors or angiotensin-receptor blockers), are required to have an extra blood test to measure potassium 1 week after starting trial treatment.

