### Statistical analysis

All analyses will be conducted according to a detailed statistical analysis plan. Analyses will be adjusted for site and the use of baseline, licensed medication for IPF. The analysis populations are defined as intention-to-treat (all randomised individuals regardless of adherence), per-protocol (all randomised individuals who adhere to the trial medication to within 80% (based on pill counts)), modified-per-protocol (all randomised individuals who adhere to the high-dose regimen) and safety population (all patients randomised who received at least one dose of the trial treatment). Non-compliance will be dealt with using a Compliance-Adjusted-Causal-Effect (CACE) analysis, using compliance data from returned medication (pill counts).

The primary outcome will be analysed using a Cox proportional hazards model adjusted for the variables included in the minimisation algorithm (baseline licensed IPF medication and site). The results will be presented as the Kaplan-Meier estimate of the survival function for each treatment arm separately and, if appropriate, the median will be estimated. The treatment effect size will be the hazard ratio and estimated with 95% confidence intervals and *p* values.

At each relevant time point from 6 weeks post randomisation, the K-BILD, EQ5D, LCQ, spirometry (FVC per cent predicted, FEV per cent predicted, FVC absolute value, FEV absolute value and FVC/FEV ratio) and DLCO will be analysed using linear model to compare the average values between the treatment arms adjusted for the variables included in the minimisation algorithm: baseline disease-modifying therapy and site will be included as a random effect. The effect size will be the mean difference and will be presented with 95% confidence intervals and *p* values.

The MRC Breathlessness Score and cough score will be analysed using a Mann-Whitney test to compare the distribution of the score between the treatment arms. A generalised effect size will be estimated and presented with 95% confidence intervals and *p* values.

The safety analysis will be based on the pre-defined population (as above). Summary tables will be presented for incidence rates (number of patients with at least one incidence) of adverse events and serious adverse events coded according to the Medical Dictionary for Regulatory Activities (MedDRA). Tables of change from baseline will be presented for the blood and other clinical laboratory assessments.

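### Deaths and admissions reach the serious-event table only if attributed to drug, and adverse-event counts and the stated treatment period overlook that treatment stops at the first primary event

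*Protocol article*

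**What the plan says.** All references are to the protocol article.

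- **Classification.** The Adverse events section rules: "As hospitalisation and death are outcome variables they will only be regarded as serious adverse events if they are drug related".
- **Safety tables.** The Statistical analysis section plans MedDRA-coded tables of "incidence rates (number of patients with at least one incidence) of adverse events and serious adverse events", in everyone who took at least one dose, plus laboratory changes from baseline. It puts no relatedness filter on ordinary adverse events and gives no person-time denominator.
- **Stopping of treatment.** Methods/design says: "Participants receive co-trimoxazole or placebo until they meet a primary endpoint event", or until consent is withdrawn or the trial ends.
- **Stated duration.** The same section describes the trial "with outcomes assessed over a median treatment period of 27 (range 12–42) months". The Abstract and Interventions also call this a treatment period, while Sample size presents 27 months as the median time a patient spends in the trial.
- **Capture of events.** Methods/design commits to collecting vital status and admission details for every consenting patient, including those who withdraw. The Abstract says the primary outcome "will be determined from adverse event reporting, hospital databases and the Office of National Statistics", with active tracing.
- **Outcome analyses.** Primary outcomes and Secondary outcomes compare all-cause death, transplant and first non-elective admission by arm, together and as components, and separate respiratory from non-respiratory events.
- **Known hazard.** Patient characteristics records: "A risk of sudden death in patients treated with co-trimoxazole and angiotensin-converting enzyme (ACE) inhibitors was identified", and links it to raised potassium.

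**The concern.** A randomised comparison of serious events needs no judgement about cause, because the placebo arm supplies the background rate. The rule in Adverse events brings that judgement back for the two most serious kinds of event. It goes further than an exemption from expedited reporting, since it changes what counts as a serious adverse event. It also covers hospitalisation without qualification, although only the first non-elective admission is an outcome.

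The hazard that the article itself names makes this matter. A sudden death or collapse in a frail patient with advanced IPF could plausibly be put down to the disease. It would then not enter the coded serious-event table. It would count in the primary outcome, but there the finest breakdown is respiratory versus non-respiratory. Fewer respiratory admissions could offset more arrhythmic or hyperkalaemic events in the composite.

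Separately, if treatment stops at the first primary event, the arm with fewer events stays on treatment longer. A count of patients with at least one adverse event then mixes the adverse-event rate with the efficacy result. The same stopping rule means that the stated treatment period cannot be right as a description of time on drug.

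**Working it through.** **1. Which analysis shows which event**

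| Event judged unrelated to drug | Serious-event table | Outcome analyses |
|---|---|---|
| Death | No | Yes, respiratory/non-respiratory only |
| First non-elective admission | No | Yes, respiratory/non-respiratory only |
| Later non-elective admission | No | Not in the time-to-first analysis |
| Elective admission | No | No |

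The article does not say whether such events are coded and tabulated as ordinary adverse events.

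**2. Inputs (Sample size)**

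Medians are 28.8 months (placebo) and 51.1 months (active). Accrual is 30 months with 12 more months of follow-up, so potential follow-up F runs from 12 to 42 months. Further assumptions: exponential event times, F uniform, treatment ending at the primary event, and no other discontinuation.

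**3. The plan's own figure**

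The hazard ratio is 28.8/51.1 = 0.5636. Schoenfeld's formula gives 4 × (1.960 + 0.842)² / (ln 0.5636)² = 96 events after rounding up, with power 0.802. The stated 96 events reproduce.

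**4. Time on treatment**

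Hazards: λ = ln 2/28.8 = 0.02407 and ln 2/51.1 = 0.01356 per month.

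Probability of a primary event: P = 1 − [exp(−12λ) − exp(−42λ)]/(30λ).
- Placebo: 1 − (0.7492 − 0.3639)/0.7220 = 0.466.
- Active: 1 − (0.8498 − 0.5657)/0.4069 = 0.302.

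Mean time on treatment = P/λ.
- Placebo: 19.4 months.
- Active: 22.3 months.
- Ratio: 1.15. With no treatment effect it is 1.0.

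Median time on treatment solves exp(−λt) × (42 − t)/30 = 0.5.
- Placebo: 18.6 months.
- Active: 21.8 months.

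Stopping before month 12: 1 − exp(−12λ).
- Placebo: 25%.
- Active: 15%.

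By contrast, 27 = 12 + 30/2 is the median of F itself, which is potential follow-up.

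**5. Effect on the crude count**

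Suppose the adverse-event rate r on treatment is the same in both arms and events are counted only on treatment. The probability of at least one event is the average over F of r/(r + λ) × [1 − exp(−(r + λ)F)]. The article gives no rates, so r is assumed over a range. The last column assumes instead that active treatment raises the endpoint hazard by the inverse ratio (mean time on active 15.5 months). Ratios use unrounded proportions.

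| r per patient-year | Placebo | Active, HR 0.5636 | Ratio | Ratio if the drug harms |
|---|---|---|---|---|
| 0.1 | 0.146 | 0.166 | 1.14 | 0.81 |
| 0.2 | 0.264 | 0.299 | 1.13 | 0.82 |
| 0.5 | 0.508 | 0.564 | 1.11 | 0.84 |
| 1.0 | 0.712 | 0.773 | 1.08 | 0.88 |

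The true rate ratio is 1 throughout. Under benefit the count makes the drug look worse. Under harm it makes the drug look safer.

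**6. Number of patients concerned**

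With 330 patients, 165 × (0.466 + 0.302) ≈ 127 would have a primary event under this model. With 264 the model gives about 101, against the 96 stated. These events are analysed as outcomes and are not lost data.

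**The case against.** A reader might infer that the endpoint source contradicts itself, because the Abstract relies on adverse event reporting while Adverse events excludes most deaths and admissions. The article does not support that. The Abstract names adverse event reporting, not serious adverse event reporting, and lists other sources beside it. The Adverse events rule governs classification, not recording, and Methods/design captures deaths and admissions for everyone. At most, the route by which an unrelated admission is recorded deserves a sentence.

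A reader might also infer that the safety tables cannot show unattributed harm at all. That is too strong. Ordinary adverse events are tabulated without a stated relatedness filter, and laboratory changes are tabulated. Electrolytes are checked from week 6, and patients at risk from raised potassium are excluded or monitored more closely. There is an independent data monitoring committee. An all-cause excess of deaths or first admissions would appear by arm in the outcome analyses.

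Other fair points:
- Blinding makes attribution errors more likely to dilute a signal than to favour one arm. This stands, but dilution is itself the problem for a rare, cause-specific harm.
- Counting patients with at least one event is conventional, and an analysis plan not shown may add exposure-adjusted rates or cause tables. This stands as to silence. The classification rule and the definition of incidence, however, are written in the article.
- The exposure ratio of 1.15 needs the full planned effect, and no on-treatment window for adverse events is stated. Both points stand and limit the size claimed.
- No stated analysis uses 27 months as exposure. True, but the figure is still wrong as a treatment period.

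**Conclusion.** The point holds in three limited parts and should be changed. It does not threaten the primary analysis.

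1. The serious-event table depends on attribution for deaths and hospitalisations. A cause-specific excess, such as arrhythmic or hyperkalaemic events, or an excess of admissions after the first, would otherwise be seen only through that attribution or a coarse respiratory split. How often attribution would fail cannot be estimated from the article.
2. The incidence summary is a patient count, while exposure depends on outcome. Under the planning medians, mean exposure differs by a factor of 1.15, and equal adverse-event rates give a crude ratio of about 1.08 to 1.14 for assumed rates of 0.1 to 1.0 per patient-year. With no treatment effect there is no distortion. The crude ratios also assume that adverse events are counted only while on treatment.
3. The stated treatment period of 27 (12–42) months is potential follow-up. Under the stopping rule, expected median treatment is about 18.6 months on placebo and 21.8 on active. About 25% and 15% stop before month 12, so the range cannot begin at 12. Withdrawals or other discontinuation would shorten these times further.

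**What to change.** - Keep any exemption of expected outcome events from expedited reporting. Add a table, for the data monitoring committee and the final report, of all deaths and non-elective admissions by arm and MedDRA-coded cause, regardless of attributed relatedness. Include admissions after the first, and show drug-related events as a subset.
- Add one sentence on how a death or admission judged unrelated is recorded and reaches the endpoint data.
- Beside the count of patients with at least one event, give adverse-event rates per patient-year on treatment by arm, and state the period over which events are counted.
- In the Abstract, Methods/design and Interventions, describe 27 (12–42) months as potential follow-up, so that it agrees with Sample size and the stopping rule. Report observed time on treatment separately.

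The deaths and admissions are already captured under Methods/design. The cost is coding their causes, an extra table and some rewording, with no new visits.

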### Sample size

With 264 patients predicted to be randomised over a period of 30 months and an additional 12-month follow-up after the last patient is recruited (a total of 42 months after the first patient is enrolled, median patient trial duration of 27 months) we expect 96 primary endpoint events to occur uniformly over the duration of the trial. This will have 80% power (two-sided test, significance level of 5%) to show a change in hospitalisation-free survival from a median value of 28.8 months in the control arm to 51.1 months in the co-trimoxazole arm (hazard ratio of 0.56) using a log-rank test. This is based on a sensitivity analysis of all patients from TIPAC (including IIP and/or IPF) with reduced lung function (FVC < 75% predicted) using an intention-to-treat analysis.

### Statistical analysis

All analyses will be conducted according to a detailed statistical analysis plan. Analyses will be adjusted for site and the use of baseline, licensed medication for IPF. The analysis populations are defined as intention-to-treat (all randomised individuals regardless of adherence), per-protocol (all randomised individuals who adhere to the trial medication to within 80% (based on pill counts)), modified-per-protocol (all randomised individuals who adhere to the high-dose regimen) and safety population (all patients randomised who received at least one dose of the trial treatment). Non-compliance will be dealt with using a Compliance-Adjusted-Causal-Effect (CACE) analysis, using compliance data from returned medication (pill counts).

The primary outcome will be analysed using a Cox proportional hazards model adjusted for the variables included in the minimisation algorithm (baseline licensed IPF medication and site). The results will be presented as the Kaplan-Meier estimate of the survival function for each treatment arm separately and, if appropriate, the median will be estimated. The treatment effect size will be the hazard ratio and estimated with 95% confidence intervals and *p* values.

At each relevant time point from 6 weeks post randomisation, the K-BILD, EQ5D, LCQ, spirometry (FVC per cent predicted, FEV per cent predicted, FVC absolute value, FEV absolute value and FVC/FEV ratio) and DLCO will be analysed using linear model to compare the average values between the treatment arms adjusted for the variables included in the minimisation algorithm: baseline disease-modifying therapy and site will be included as a random effect. The effect size will be the mean difference and will be presented with 95% confidence intervals and *p* values.

The MRC Breathlessness Score and cough score will be analysed using a Mann-Whitney test to compare the distribution of the score between the treatment arms. A generalised effect size will be estimated and presented with 95% confidence intervals and *p* values.

The safety analysis will be based on the pre-defined population (as above). Summary tables will be presented for incidence rates (number of patients with at least one incidence) of adverse events and serious adverse events coded according to the Medical Dictionary for Regulatory Activities (MedDRA). Tables of change from baseline will be presented for the blood and other clinical laboratory assessments.

Requests for access to trial data and stored samples will be considered, and approved in writing where appropriate, after formal application to the TMG and TSC.

Full details of the analysis will be finalised in an analysis plan before database lock.

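### The primary Cox model omits baseline FVC and DLCO, which the trial measures and treats as prognostic, so it forgoes some power and leaves chance imbalance uncorrected

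*Protocol article*

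**What the plan says.** In the protocol article, Statistical analysis gives a general rule, "Analyses will be adjusted for site and the use of baseline, licensed medication for IPF". It then names the same two variables again for the primary Cox model, on the ground that they are the minimisation variables. The section on identification, recruitment and randomisation confirms that lung function is not a minimisation factor.

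Elsewhere the article treats lung function as prognostic:

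- Lung function: "FVC and DLCO are both components of prognostic modelling algorithms".
- Patient characteristics: the upper FVC limit for entry is there partly "to identify patients more likely to meet the primary endpoint".
- Secondary outcomes: the measurement schedule that covers spirometry and DLCO starts at baseline.

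The Sample size section plans the comparison "using a log-rank test", with no covariates: "we expect 96 primary endpoint events to occur uniformly over the duration of the trial". No section says why FVC and DLCO are left out of the primary model.

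**The concern.** FVC and DLCO are neither balanced by the randomisation nor adjusted for in the primary analysis. The only patient-level covariate is an indicator of IPF medication; the other covariate is site.

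In a Cox model, leaving out a variable that predicts the outcome has two consequences. The hazard ratio estimated without it lies closer to 1 than the hazard ratio conditional on it, and the test is less powerful than the adjusted test on the same data. A chance difference between arms in lung function also passes straight into the treatment estimate. If such a difference appeared, an adjustment chosen after unblinding would carry little weight.

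**Working it through.** **Inputs from the Sample size section.** Medians 28.8 and 51.1 months, two-sided 5% level, 80% power, 96 events, 264 patients, 30 months of accrual. Allocation is 1:1 (Methods/design). The article gives no hazard ratio per SD for FVC or DLCO, so I assume 1.25 to 2.0 per SD of one combined FVC/DLCO score.

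**Step 1: the plan's own figure.** The hazard ratio is 28.8/51.1 = 0.5636, and its log is −0.5734. By Schoenfeld's formula:

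- Events = 4(1.960 + 0.842)²/(0.5734)² = 31.40/0.3288 = 95.5, rounded up to 96.
- Power at 96 events = Φ(√96/2 × 0.5734 − 1.960) = Φ(0.849) = 80.2%.

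The stated 96 events and 80% power reproduce. With the rounded hazard ratio of 0.56 the formula gives 94 events, and 81.1% power at 96.

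**Step 2: what adjustment would add.** I simulated trials of 264 patients, 132 per arm, with exponential survival, uniform accrual over 30 months, one standard normal prognostic score, and analysis at the 96th event. Each simulated trial was analysed by a Cox model with and without the score. There were 5,000 trials per setting for the marginal reading and 3,000 for the conditional one. The Monte Carlo error of each power is about 0.6 to 0.9 points.

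The answer depends on what 0.56 means. In the marginal reading, the conditional hazard ratio was tuned (to 0.558, 0.549, 0.542 and 0.520) so that the unadjusted estimate averaged 0.555 to 0.564. In the conditional reading, 0.5636 is the effect at a fixed value of the score.

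| Assumed HR per SD | Marginal: power without / with score | Gain (points) | Conditional: power without / with score | Gain (points) |
|---|---|---|---|---|
| 1.25 | 78.7% / 79.3% | 0.6 | 77.6% / 78.6% | 0.9 |
| 1.5 | 80.4% / 82.6% | 2.2 | 75.5% / 78.3% | 2.8 |
| 1.75 | 79.3% / 84.6% | 5.3 | 73.7% / 78.7% | 5.0 |
| 2.0 | 80.9% / 88.4% | 7.5 | 69.8% / 78.7% | 8.9 |

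(Conditional gains are taken before rounding.) With a score of no prognostic value, power is 81.3% either way, so nothing is lost by adjusting. In the conditional reading the average unadjusted hazard ratio moves from 0.558 with no prognostic score to 0.566, 0.578, 0.584 and 0.595 down the rows. That is the expected pull towards 1.

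**Step 3: chance imbalance.** With 132 per arm, the standard error of the difference in mean score is √(2/132) = 0.123 SD, so the ordinary 95% limit is 1.96 × 0.123 = 0.24 SD. Left uncorrected, an imbalance of that size multiplies the treatment hazard ratio by exp(0.24 × ln 1.5) = 1.10 or exp(0.24 × ln 2) = 1.18. A hazard ratio of 0.56 would then show as about 0.62 to 0.66. On the log scale the shift is 0.10 to 0.17, against a standard error of 2/√96 = 0.20, so about half to four-fifths of a standard error.

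**The case against.** The strongest reply is that nothing here is wrong or contradictory. Adjusting for the minimisation factors matches the analysis to the design, the covariates are pre-specified, and the planned power holds for the planned test. All of that stands.

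A reader might go further and infer from the table that the trial really has about 70% power, or that the sample size should be raised. The documents do not support this. The 0.56 comes from whole-arm medians and a log-rank test, so variation between patients is already inside it and it reads as a marginal hazard ratio. On that reading unadjusted power stays at 78.7% to 80.9% over the whole assumed range. The lower figures appear only if 0.56 is taken as conditional.

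The second reply is that the prognostic strength is unknown and may be modest. This stands in part:

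- Entry is capped at an FVC of 75% predicted, which narrows the spread of FVC.
- Protocol amendments says that raising the cap from 70% was not expected to lower the event rate.
- The article does not say which outcome the prognostic algorithms predict, whereas the primary endpoint includes all-cause unplanned admission.

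FVC alone may therefore sit at the low end of the range. The article describes no entry limit on DLCO. In the other direction, the Discussion cites annual mortality of 8% in trials of mild-moderate patients and 19% in trials including moderate-severe patients. That comparison is across studies and for death only, so it does not give a hazard ratio per SD.

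Third, the SAP is not shown and may contain an adjusted sensitivity analysis, so it cannot be said that none is planned. The primary covariate set, however, is stated outright and is not left to the SAP.

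Last, the simulation is a best case. It has one correctly specified score, no site terms and no missing values.

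**Conclusion.** The point holds as forgone efficiency and uncorrected chance imbalance. It is not a sample-size error, and the primary test is not invalid: the chance imbalance in Step 3 does not bias the estimate on average, and the unadjusted test already allows for it.

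The forgone gain is about 1 to 8 points of power if 0.56 is marginal, or about 1 to 9 if it is conditional. Both ranges rest on an assumed hazard ratio of 1.25 to 2.0 per SD of a combined score, for which the documents give no figure. If the true strength is near the bottom of that range, the gain is negligible.

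The case rests on FVC and DLCO alone. A reader might want to add age, but the article nowhere calls age prognostic for this endpoint. I rate the point a cheap improvement.

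**What to change.** Before database lock, when the article says the analysis plan will be finalised, and before unblinding:

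- Name baseline FVC % predicted and baseline DLCO as continuous covariates in the primary Cox model, alongside licensed IPF medication and site.
- State a simple imputation for missing baseline DLCO that uses baseline data only, so that no randomised patient drops out of the primary analysis.
- Report the model with the minimisation factors only as a sensitivity analysis.
- Say that the primary hazard ratio is conditional on the listed covariates.

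The cost is wording in the SAP and two more parameters, with no new data collection. The downsides are small: the reported hazard ratio becomes conditional on lung function, so it is not exactly the quantity used in the power calculation, and some baseline DLCO values will have to be imputed.
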